##### RS-fMRI Analyses

RS-fMRI will undergo two types of analyses in the CONN toolbox: (1) ROI-to-ROI analyses (using the ROIs listed in Table 1), and (2) a whole-brain independent component analysis (ICA). For the ROI analyses, region-to-region connectivity (z-matrix) will be extracted using the 210 V Maximum Probability Map parcellation method (Glasser et al., 2016). The z-matrix will be sorted and undirected adjacency matrices will be defined with varying cost (1–50%). For example, at 25% cost threshold, the top 25% of the z-values will be set to 1 and the rest set to 0, excluding the diagonal elements. Global graph theory metrics (e.g., characteristic path length, clustering coefficient, smallworldness, global efficiency and mean local efficiency) will be compared between groups (Watts and Strogatz, 1998; Humphries and Gurney, 2008; Rubinov and Sporns, 2010). Degree centrality (DC) refers to the number of regions that are functionally connected to a region—this is an appropriate connectivity metric for the dlPFC in PD as this region is important in top-down cognitive control. Betweenness centrality (BC) refers to the number of times a region (i.e., node) is along a shortest path between region-pairs and thus is a suitable connectivity metric to assess convergent neuroanatomical structure, such as the caudate nucleus (Alexander et al., 1986). Both DC and BC will be computed at a regional level. Recently, we demonstrated that DC of the left dlPFC correlates with inhibition control performance in normal healthy individuals (unpublished pilot data) while the BC level of the caudate correlates with cognitive performance in non-demented PD patients (Wright et al., 2020).

For the whole-brain analyses, data will be run through an ICA in CONN, which separates the RS-fMRI data into components, with the signal of these components being maximally independent from each other (Calhoun et al., 2009). The components separated using ICA tend to separate into groups, comprising highly replicable resting state networks: regions whose activity is correlated over time, in the absence of a task. Several resting state networks of interest will be investigated in pre- vs. post-intervention, including the central executive, sensorimotor, visual, default mode, and cerebellar networks, as these networks are related conceptually to the motor and cognitive deficits observed in PD and many have been shown to be altered in PD in the past (de Schipper et al., 2018; Wolters et al., 2019; Dong et al., 2020; Schneider et al., 2020).

##### pCASL Analysis

For the pCASL images, the preprocessed cerebral blood flow (CBF) images will be assessed using SVM-ISDA, which will be used to train a classifier that separates patients into PD patients with normal cognition, and those with mild cognitive impairment. The pCASL data will be analyzed by Machine-based Alzheimer’s disease Designation (MAD) to compute Alzheimer’s-like pattern expression scores (Katako et al., 2018). High scores in metabolic/perfusion patterns indicate similarity with Alzheimer’s patients—we have previously shown that PD dementia patients show similar brain metabolic patterns and that perfusion imaging may replace FDG-PET imaging when MAD is applied (Katako et al., 2018). Our recent work suggests the utility of using SVM-ISDA-based scores for monitoring disease progression in repeated measures designs. Changes in these scores will be used to assess the neural correlates of the treatment response.

##### DTI Analysis

Diffusion tensor imaging data will be preprocessed using SPM12 and the artifact correction in diffusion MRI toolbox (ACID;^5^
RRID:SCR_010470)) and after coregistration of each participant’s diffusion weighted data with their T1w image, data will undergo eddy current and motion correction, before fitting the diffusion tensor, using an ordinary least squares algorithm. CAT12 will be used for segmentation and skull stripping of the b0 map. Fiber tracking, fractional anisotropy (FA), axial diffusivity (AD), radial diffusivity (RD), and mean diffusivity (MD) map creation will be done using the ACID toolbox. ROIs [e.g., forceps minor, corpus callosum, uncinate fasciculus, and cingulum (Ghanavati et al., 2018; Snir et al., 2019)] will be investigated.

## Anticipated and Preliminary Results

The anticipated results of this study can be broken down by objective. First, in comparing if and how metabolic brain activity differs during single and DT-walking in PD patients, compared to able-bodied controls, we will likely observe increased activation of sensorimotor and cerebellar brain regions and decreased activation in the PFC of the PD patients. We hypothesize that these changes in brain activation patterns will be associated with decreased gait and cognitive performance measures and the magnitude of DT effects. Second, we hypothesize that both training programs will result in significant improvements in gate and cognitive function with medium to large effect sizes, and that the DT training program will result in significantly greater improvements in the XG compared to CG, also with medium to large effect sizes. It is hypothesized that the DT treadmill-training program will result in specific and significant changes of the DT gait-related abnormal brain metabolic pattern observed in Objective 1.

Our behavioral and PET hypotheses are supported by a recent feasibility study that we completed in which 15 PD patients (Hoehn and Yahr stages II-III) participated in a 10-week DT-treadmill gait training program using the VMT and VCG as described in the “Methods” section above (Mahana et al., 2021). Significant improvements in the majority of gait variables (average and COV of SL and SW) with medium to large effect sizes were observed following the intervention. This was the case for both walk-only and DT-walking assessments. There were also significant improvements in VMT and VCG outcome measures post-intervention with medium to large effect sizes. This was the case when tested while sitting and while treadmill walking. In addition, a qualitative analysis of the participant’s experiences revealed that the program was challenging and required a high degree of mental processing. The majority of participants reported that the games were engaging and they appreciated the variety of games used for the DT training. Also, to note 3 of the 15 participants did not like playing the games.

In a recent pilot study, we tested the feasibility of imaging the DT-walking-related changes in brain glucose metabolism in patients with PD (Szturm et al., 2020). Fifteen patients with PD (stage II and III) were scanned with FDG-PET. Ten patients were rested during the FDG uptake period and five patients performed DT treadmill walking for 28 min. All five PD patients receiving the DT-walking protocol showed a consistent DT interference of gait measures (average and COV) and of all VMT and VCG performance measures. Glucose metabolism was significantly increased in several brain regions of the patients who performed the DT treadmill walking as compared to those who rested during the uptake period. These regions include primary visual/sensorimotor areas, thalamus, superior colliculus, and cerebellum. When individual results were analyzed, patients in the earlier stage of PD (Hoehn and Yahr stage II) showed increased FDG uptake in the PFC regions during DT treadmill walking as compared to resting levels. More progressed PD patients (Hoehn and Yahr stage III) did not show any notable increase in PFC activity during DT treadmill walking. It should be also noted that patients with mild cognitive impairment (MCI) also show suppressed PFC activity during walking (Holtzer and Izzetoglu, 2020).

In regards to the pilot MRI data, we expect significant neural changes across modalities. Due to the importance of the dorsolateral PFC for both cognition and gait, we expect both PD groups to have reduced functional connectivity between this region and other basal structures compared to able-bodied controls using RS-fMRI data (Monchi et al., 2004; Nagano-Saito et al., 2014). We expect that following intervention, the XG group will have increased functional connectivity between these regions compared to the CG group, and that this functional connectivity will correlate with PD stage. Similarly, in the whole-brain RS-fMRI analysis, we hypothesize that pre-intervention, both PD groups will have altered functional connectivity within central executive, sensorimotor, visual, default mode, and cerebellar resting state networks compared to healthy controls (de Schipper et al., 2018; Wolters et al., 2019; Dong et al., 2020; Schneider et al., 2020), but that PD groups will not differ from each other. Post-intervention, we hypothesize that functional connectivity within these networks will differ between XG and CG PD groups. For the pilot pCASL data, we hypothesize that SVM-ISDA scores will not differ between PD groups at baseline, but will differ from able-bodied controls. Following intervention, we hypothesize that scores for both XG and CG groups will be reduced, with a larger effect observed for the XG group, indicating a larger treatment response. Although the DTI data are largely pilot data in nature, based on previous research indicating that reduced white matter integrity in forceps minor, corpus callosum, uncinate fasciculus, and cingulum is associated with reduced gait stability and may be associated with an increased risk of falling (Ghanavati et al., 2018; Snir et al., 2019), we hypothesize that the same relationship will hold in our sample. While it is thus far unclear whether structural changes in DTI can be observed in our population following 10-weeks of intervention, we expect that increased white matter integrity at post-intervention will be associated with improved gait stability and reduced number of falls at the 6-month follow-up.

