### Participants

52 patients with PD [26 from Winnipeg, MB, Canada (site 1) and 26 from Toronto, ON, Canada (site 2)], and 15 age-matched healthy, able-bodied control subjects (site 1) will be recruited in a 2-year time period. The criteria used for recruitment of the patients will include; (a) diagnosis of PD according to United Kingdom brain bank criteria (Hughes et al., 1992), (b) stage II-III of PD according to the Hoehn and Yahr scale (Bhidayasiri and Tarsy, 2012), (c) age 50–75 years, (d) adequate vision to see required images on a standard computer monitor, (e) able to score 26 or greater on the Montréal cognitive assessment scale [MoCA (Marinus et al., 2011)], (f) on stable medications for the past 3 months, and (g) able to walk overground for 2 min without an aid or cane. The exclusion criteria for participation will include the following: (a) diagnosis of any psychiatric comorbidity or history of any other neurological disease other than PD, (b) any other medical condition limiting participant ability to walk on the treadmill, and (c) neuroimaging contraindications (i.e., claustrophobia, severe dyskinesia, diabetes, non-compatible metal implants, etc.). Healthy able-bodied adults with the same inclusion/exclusion criteria listed above except for diagnosis of PD will be recruited.

All responders to calls for participation will undergo a screening assessment. Ethics approval has been obtained from the institutional Human Research Ethics Boards. All volunteer participants will be asked to read and sign the informed consent form. The Clinical trial has been registered at ClinicalTrials.gov, identifier: NCT04415775.

Successfully screened PD participants will be randomized to the experimental intervention (XG) or an active control arm (CG). A computerized block randomization procedure will be implemented by an independent statistician. Randomization will be stratified by stage of the disease (Hoehn and Yahr stage II and III). To ensure similar representation of men and women, randomization will also be stratified by sex. Randomization will be achieved by having participants choose an opaque sealed envelope, each containing a group assignment.

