#### Statistical Analyses

Our sample size was calculated based on our previous work involving PET imaging in PD in which participants were randomized into either gene therapy or sham-surgery groups, and assessed at 6 months follow-up (Ko et al., 2014a). With anticipated ρ2 = 0.673 [20% more than what is expected for placebo effect-related pattern’s explanation of clinical benefits induced by sham surgery over 6-months (Ko et al., 2014a)], G^∗^Power (version 3.1.9.2; RRID:SCR_013726) estimates the minimal sample size to be 12 (effect size f2 = 2.060). With maximally anticipated drop-out rate of 10% (e.g., motion artifacts, patient’s voluntary withdrawal, etc.); we require 13 subjects per group/site.

MATLAB (The Math Works Inc., Natick, MA, United States version 2010a) will be used to compute the outcome measures. Normality of the data will be assessed using the Shapiro-Wilks test. Sphericity will be assessed using Mauchly’s test. For normally distributed data sets, a mixed-model ANOVA will be used to examine the effects of time (pre– and post-intervention), group (XG and CG) and interaction of time^∗^group of all behavioral outcome measures (gait, cognitive, neuropsychological, fall rates, physical activity levels, and health-related quality of life). Note the time factor for fall rates, physical activity outcome measures, and health-related quality of life will include the 6-month and 12-month follow-up time periods. Non-normally distributed data will be assessed using the Wilcoxon-Signed rank test to determine differences between pre- and post-intervention. The significance level will be set at *p* < 0.05, and statistical analysis will be conducted using SPSS (v.22; SPSS Science, Chicago, IL, United States).

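### Baseline MRI hypotheses are worded by randomised arm, and two predict that the arms will not differ; the pre-training disease contrast should pool the arms and account for scanner

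*Protocol article*

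**What the plan says.** The Participants section plans 52 PD patients, 26 at each of two sites, randomised to the dual-task arm (XG) or the active control arm (CG), and "15 age-matched healthy, able-bodied control subjects (site 1"). The Statistical Analyses section says "we require 13 subjects per group/site", which gives 26 patients per arm over two sites. MRI is acquired before training in everyone and after training in PD patients only.

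The Anticipated and Preliminary Results section makes three statements on the pre-training MRI data that concern the PD groups:

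- Dorsolateral prefrontal connectivity (RS-fMRI): "we expect both PD groups to have reduced functional connectivity between this region and other basal structures compared to able-bodied controls".
- Five resting-state networks (RS-fMRI): "both PD groups will have altered functional connectivity within central executive, sensorimotor, visual, default mode, and cerebellar resting state networks compared to healthy controls", followed by "but that PD groups will not differ from each other".
- pCASL pattern score: "SVM-ISDA scores will not differ between PD groups at baseline, but will differ from able-bodied controls".

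For PET the article is worded differently. The first objective, the Aim 1 paragraph under Statistical Analyses and the pre-intervention pattern under FDG-PET Analysis all treat PD as one group. The same Aim 1 paragraph assigns the patient-control comparison to PET. It gives MRI the pre/post comparison, by paired t-tests. The RS-fMRI Analyses section compares graph metrics between groups without saying which groups.

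The Neuroimaging Equipment section gives Winnipeg (site 1) a Siemens 3-Tesla MRI scanner and Toronto (site 2) a GE 3-Tesla scanner.

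**The concern.** Randomisation settles how the two arms relate before treatment: they are samples from one population, and the arm label says nothing about a scan taken before the first session. Two consequences follow if the hypotheses are analysed as worded.

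First, the disease contrast is made with part of the available patients, so it is less precise than it need be. Second, the statement that the arms will not differ is a null hypothesis already known to be true of the allocation process. A significant result would be a chance finding. A non-significant result would be read as evidence of comparability that a sample of this size cannot give.

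For RS-fMRI and pCASL, the anticipated-results section is the only place where the article words the patient-control contrast, so its wording is what an analyst would follow. At stake is the sensitivity and interpretation of the pilot MRI disease contrast, not the treatment comparison.

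**Working it through.** **Inputs from the article.** 52 PD patients, 26 per site; 15 controls, all at site 1; 13 per group per site. Check: 13 × 2 sites = 26 per arm, and 26 × 2 arms = 52, which agrees with the Participants section. At site 1 there are therefore 26 patients, 13 per arm.

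**Assumptions.** The article gives no patient-control effect size for RS-fMRI or pCASL, so a standardised difference d of 0.5 to 1.2 is used. It sets the significance level at 0.05 without stating sidedness, and in the context of the behavioural analyses. Two-sided 0.05 is assumed for imaging.

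**1. Precision of PD minus controls (in SD units).** SE = √(1/n_PD + 1/n_control).

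- Both arms, both sites: √(1/52 + 1/15) = 0.293
- One arm, both sites: √(1/26 + 1/15) = 0.324
- Both arms, site 1: √(1/26 + 1/15) = 0.324
- One arm, site 1: √(1/13 + 1/15) = 0.379

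The first two lines treat the scanners as interchangeable. With a scanner term in the model, site 2 has no controls, so the contrast comes essentially from site 1 and the last two lines apply.

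**2. Power.** Two-sample t-test, noncentral t with n_PD + 15 − 2 degrees of freedom and noncentrality d/SE.

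| d (assumed) | Pooled, both sites, no scanner effect (52 vs 15) | Pooled, site 1 (26 vs 15) | One arm, site 1 (13 vs 15) |
|---|---|---|---|
| 0.5 | 39% | 33% | 25% |
| 0.6 | 52% | 44% | 33% |
| 0.8 | 77% | 67% | 53% |
| 1.0 | 92% | 85% | 72% |
| 1.2 | 98% | 95% | 86% |

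The 26 vs 15 column also gives the power for one arm over both sites if scanner effects are ignored. On either basis, splitting costs power at every d in the range. At d = 0.8 it falls from 67% to 53% within site 1, or from 77% to 67% if the scanners can be combined freely.

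**3. Baseline arm versus arm, 26 vs 26.**

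- The true difference is zero by design, so each test rejects in 5% of trials. Over five networks, if independent, at least one rejects in 1 − 0.95⁵ = 22.6% of trials.
- The 95% CI half-width is t(0.975, 50) × √(2/26) = 2.009 × 0.277 = 0.56 SD. A non-significant result is therefore compatible with observed imbalances of about half an SD. Power against a 0.5 SD imbalance would be 42%.

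**The case against.** The strongest reply is that the wording sits among anticipated results for data the article calls pilot, and that none of the analysis sections specifies a by-arm baseline test. Saying that both groups should look abnormal and should resemble each other can be a plain description of the expected pattern. No baseline result triggers an adjustment or exclusion, Objective 1 is a PET objective that already treats PD as one group, and the sample size rests on PET. All of this stands, and it makes the point minor. It does not remove it, because the no-difference statements are put forward as hypotheses and the article words the MRI disease contrast nowhere else.

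Four stronger readings are tempting and not supported.

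- **Both arms must be significant against controls.** This would give 54% power at d = 0.8 for two comparisons of 26 vs 15, but no joint-significance rule is written anywhere.
- **All three statements share the full structure.** Only the five-network sentence does. The prefrontal sentence has no clause about the arms being alike, and the control part of the pCASL sentence can be read as a pooled comparison. The DTI expectation is not split by arm.
- **Pooling yields 52 vs 15 at no cost.** That ignores the scanner layout. Pooling over sites without a scanner term would mix disease with scanner.
- **The treatment comparison is biased.** Nothing in the article makes the post-training contrast depend on a baseline test.

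**Conclusion.** The point holds as a minor one. The pre-training RS-fMRI hypotheses are worded by randomised arm, and for the five networks and the pCASL score the article hypothesises that the arms will not differ at baseline. Any such difference would be chance, and its absence would show little, given a half-width of 0.56 SD.

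The cost of splitting is moderate. At d = 0.8 and with scanner accounted for, it is about 14 percentage points (67% pooled against 53% for one arm). The 77% for 52 vs 15 is attainable only if scanner effects are negligible. These figures rest on the assumed d, two-sided 0.05, independent normal observations with equal variance, and equal arms of 13 per site. The 22.6% also assumes that the five networks are independent.

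**What to change.** 1. Reword the pre-training RS-fMRI and pCASL hypotheses as all PD patients, arms pooled, versus controls, as the Objectives and the Aim 1 paragraph do for PET.
2. Include a scanner/site term in that contrast, or restrict it to site 1, and say which.
3. Delete the two hypotheses that the arms will not differ at baseline (five networks; pCASL score). Show baseline values by arm descriptively, without tests.
4. Keep XG versus CG contrasts for post-training data.

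The cost is a few sentences and one model term, with no new data. The downside is that, once scanner is accounted for, the site 2 patients add little to the disease contrast, which then rests on about 26 patients and 15 controls. The by-arm wording faces the same limit with half as many patients.

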## Discussion

An integrated approach to treatment with embedded assessment of balance, gait, visuomotor, and cognition has the potential to impact both the prevention and rehabilitation of mobility limitations, and in cognitive function. Improved mobility functioning in PD directly translates to improved community ambulation, as well as increased physical activity and social participation. These benefits are known to have a significant preventative and disease-modifying impact.

New telerehabilitation technologies will likely improve clinical outcomes by making therapy more available, more motivating, and more specific and effective. While one of the pitfalls of the present study includes possible patient attrition, previous pilot-testing work showed high retention of participants, partly due to the engaging nature and low-level of adverse events related to the intervention (Mahana et al., 2021). The computerized DT platform presented in this study broadens the type of standardized visuomotor and executive cognitive activities for use for DT balance-gait training that has previously been reported. A comprehensive analysis of spatial and temporal features of steady state gait has a greater validity to measure gait performance (rhythm, pacing, and stability) as compared to gait speed alone. The use of interactive digital media provides a flexible method to produce a wide range of executive cognitive activities while performing complex motor behaviors such as walking. The types and amount of cognitive stimulation participants engage in during intervention needs to be objectively measured, and this will help clarify the potential added benefit of activities beyond physical exercise alone. Quantification of cognitive-motor interactions has the potential to be a valid non-invasive biomarker for early detection of balance-mobility limitations and cognitive decline in the early stage of disease, and with aging, although these results will not be generalizable to later stages of PD. Although participant motion is a potential pitfall for the neuroimaging data, only early-stage PD patients with controlled tremor will be recruited. Outcomes of this research will provide new insights into brain plasticity mechanisms and will accelerate further optimization and commercialization of multi-modal mobility-cognitive training applications along with accompanying smart electronic monitoring tools.

The computer game-based treadmill platform and embedded automated electronic monitoring tools were designed to transition from physiotherapy clinics to community fitness/wellness centers, as well as assisted-living complexes. Improved and cost-effective methods of screening and fall risk assessment in the community, linked with highly-effective interventions and eHealth tools, will allow more individuals with PD to have access to, and the support of, personalized, scientifically motivated rehabilitation, no matter where they are located. In addition, the availability of electronic outcome measures and, ultimately, the creation of a web-based portal, will help optimize the platform and strengthen accountability.

While the focus of the present proposal is on the study of brain-behavior relationships and neuroplasticity mechanisms in PD, our DT mobility-training platform and behavioral PET and MRI brain imaging methods are directly applicable to other diseases that affect gait and cognition (e.g., cognitive vascular impairment, Alzheimer’s disease, and aging).

